## Abstract

**Background:**

Randomised controlled trials (RCTs) evaluating ectopic pregnancy have reported many different outcomes, which are themselves often defined and measured in distinct ways. This level of variation results in an inability to compare results of individual RCTs. The development of a core outcome set to ensure outcomes important to key stakeholders are collected consistently will guide future research in ectopic pregnancy.

**Study aim:**

To develop and implement a core outcome set to guide future research in ectopic pregnancy.

**Methods and analysis:**

We have established an international steering group of key stakeholders, including healthcare professionals, researchers, and individuals with lived experience of ectopic pregnancy. We will identify potential outcomes from ectopic pregnancy from a comprehensive literature review of published randomised controlled trials. We will then utilise a modified Delphi method to prioritise outcomes. Subsequently, key stakeholders will be invited to score potential core outcomes on a nine-point Likert scale, ranging from 1 (not important) to 9 (critical). Repeated reflection and rescoring should promote whole and individual stakeholder group convergence towards consensus ‘core’ outcomes. We will also establish standardised definitions and recommend high-quality measurements for individual core outcomes.

**Trial registration:**

COMET 1492. Registered in November 2019.

## Introduction

Ectopic pregnancy (EP) occurs when the developing embryo implants in a site other than the uterine cavity endometrium and is a potentially life-threatening complication in first trimester pregnancy [1]. It is estimated to affect 1–2% of pregnancies and accounts for 75% of early pregnancy mortality, 6% of direct obstetric causes of mortality in Australia, and up to 8% of maternal deaths globally [2–4]

It has the potential to affect patients not only in the acute setting but also has lasting impacts on future fertility, with only 50% women successfully having a live birth following an ectopic pregnancy [5]. The main categories of treatment fall into expectant management, medical management with methotrexate, or surgical management with a salpingostomy or salpingectomy. The approach towards counselling women with ectopic pregnancies depends not only on the woman’s clinical state, her wishes and level of compliance with treatment, but also her serum beta-hCG, ultrasonography findings and operator experience laparoscopically [1]. Clinically unstable patients with pain and bleeding may require immediate surgical management prior to formal ultrasonography.

Diagnosis has improved significantly in the last few decades, and randomised controlled trials (RCTs) remain the mainstay of assessing the effectiveness and safety of treatments. The pooling of individual RCT data is likely to provide the best evidence to inform clinical practice [6]. However, currently published data in ectopic pregnancy has reported many different outcomes of which many are defined and measured in diverse ways.

An analysis of the published literature in ectopic pregnancy found 30 RCTs primarily studying ectopic pregnancies [7]. Overall, the commonest outcome, treatment success by resolution of ectopic pregnancy was measured both with ultrasonography and serum beta-HCG levels, which used 6 different outcome measurements, ranging from <2 to 20 IU/L.

The lack of consensus and level of variation results in an inability to compare the results of individual RCTs and consequently directly impacts the usefulness of research to inform patients and clinicians in clinical practice. The development of core outcome sets allows for standardisation in outcome reporting and ultimately allows healthcare consumers to make more informed healthcare decisions in a collaborative manner with healthcare professionals.

We propose the development of a core outcome set to ensure outcomes important to key stakeholders are collected consistently, to guide future research in definite and probable ectopic pregnancy.

There is a notable difference in sonographic criteria for the diagnosis of ectopic pregnancy internationally. In literature originating from the USA, the presence of an extrauterine gestational sac with a yolk sac or embryo is required for the formal diagnosis of an EP [8]. This is compared with literature from Europe, UK and Australia, where EP is diagnosed based on the presence of an extrauterine inhomogenous mass known as the ‘blob sign’, or an extrauterine empty gestational sac, characterised by a hyperechoic ring known as the ‘bagel sign’ ([9,10]).

This core outcome set does not seek to reach consensus regarding the diagnostic or management dilemmas surrounding ectopic pregnancy and pregnancy of unknown location with suspected ectopic pregnancy. We also recognise that there are significant variations in ultrasound practice worldwide and the criteria to diagnose ectopic pregnancy are not consistently applied. In addition, ectopic pregnancy is often diagnosed based on biochemical algorithms without the pregnancy being positively identified on the scan. The purpose of this exercise is not to standardise the criteria for diagnosing ectopic pregnancy, but to provide a set of core outcome for reporting the result of interventional studies on the management of ectopic pregnancy regardless of the diagnostic criteria applied in the individual trials.

Core outcome sets are a minimum collection of data sets that are distinct, discriminatory and feasible outcomes which are routinely collected and reported in RCTs. These core outcomes would be standardised with measurement and reporting, allowing key stakeholders including individuals with lived experience, healthcare professionals and research clinicians to compare, combine and contrast results of trials [11].

### Primary outcome

To develop a core outcome set in ectopic pregnancy.

## Materials and methods

The methods have been informed by the Core Outcome Measures in Effectiveness Trials (COMET) Initiative Handbook and other core outcome set development studies relevant to women’s health. This study protocol is reported in accordance with established methodology in development of core outcome sets (Fig. 1).

**Fig. 1 Fig1:**
[figure not shown]
Methodology in development of core outcome sets

### Prospective registration

This study has been prospectively registered with the Core Outcome Measures in Effectiveness Trials (COMET) initiative; the registration number is 1492 and is available online (www.comet-initiative.org/studies/details/1492).

### Steering group

An international steering group of 25 individuals, including healthcare professionals, research clinicians and individuals with lived experience with ectopic pregnancies. This steering group has been formed through existing research networks to guide the development of this core outcome set and is composed of clinicians identifying as both research clinicians and healthcare professionals, as well as several individuals with lived experience with ectopic pregnancies who are part of patient advocacy groups.

### Scope of this core outcome set

The steering group recommends that the core outcome set should apply to RCTs, systematic reviews and clinical practice guidelines evaluating interventions for women with ectopic pregnancies.

### Identifying potential core outcomes

Potential core outcomes have been identified through a comprehensive literature review, extracting outcomes in published trials in management of ectopic pregnancy. A literature search was performed utilising PubMed with search terms ‘ectopic pregnancy’, filtered for RCTs published from 1997 to 2017. This search was filtered for studies in humans only and English language publications [7].

This initial search listed 89 studies, 30 of which were excluded for not primarily studying ectopic pregnancy and a further 25 excluded for not meeting CONSORT criteria for RCT. Four full-text studies could not be accessed during the literature review and were hence also excluded. Hence, 30 studies from 1997 to 2017 were analysed.

A total of 30 RCTs reported 13 different measurable outcomes in 4 different domains (Table 1). The commonest outcome, treatment success by resolution of ectopic pregnancy was listed in 76% (23/30) RCTs. However, it was measured with ultrasonography and with serum beta-HCG levels using 6 different outcome measurements, ranging from endpoint bHCG <2 to <20 IU/L.

**Table 1 Tab1:** Outcomes in ectopic pregnancy RCTs

	Outcome	Studies listed *N*=30 (%)
Resolution	Resolution of ectopic pregnancy	23 (76%)
	βHCG as marker of resolution	22 (73%)
	Ultrasound as marker of resolution	3 (10%)
	Tracking duration listed	12 (40%)
	Repeat intervention—medical or surgical	8 (26%)
	Resolution of clinical symptoms	5 (16%)
Complications	Haemorrhage—intra-operative or post-operative	7 (23%)
	Infection	4 (13%)
	Other surgical complications	3 (10%)
	Pain	3 (10%)
	Medication adverse effects for medical management	9 (30%)
Fertility	Spontaneous pregnancy	8 (26%)
	Conception via artificial reproductive technology	3 (10%)
	Subsequent ectopic pregnancy	1 (3%)
Patient experience	Treatment satisfaction	4 (13%)
	Length of stay	8 (26%)
	Economic impact—cost of care received	1 (3%)
	Psychological impact	1 (3%)

Less commonly listed outcomes included complications of medical or surgical management, fertility and patient experience.

The primary outcome of the RCT was listed in 73% (22/30) studies. Resolution of ectopic pregnancy was the primary outcome in 15 studies, followed by spontaneous conception in 3 studies, and treatment satisfaction in 2 studies. The remainder 2 studies analysed post-operative complications and surgical difficulty.

In addition, we will develop a comprehensive inventory of outcomes in consultation with key stakeholders including healthcare professionals, researchers and individuals with lived experience with ectopic pregnancies. The inventory will then be entered into a modified Delphi method, delivered through sequential online surveys using the Delphi survey software.

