### Trial status

This protocol is version number 6, dated on February 21, 2021, recruitment began on March 1, 2021, and all three rounds are anticipated to be completed in July 2021.

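### The literature part of the outcome inventory stops at 2017 and leaves out between 4 of 34 and 29 of 59 ectopic-pregnancy studies, although only outcome names were needed

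*Protocol article*

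**What the plan says.** The section Identifying potential core outcomes describes one PubMed search on a single term, "filtered for RCTs published from 1997 to 2017". Two further limits applied: "This search was filtered for studies in humans only and English language publications".

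The study flow is then given in three steps. First, "This initial search listed 89 studies, 30 of which were excluded for not primarily studying ectopic pregnancy". Next, "a further 25 excluded for not meeting CONSORT criteria for RCT". Last, "Four full-text studies could not be accessed during the literature review and were hence also excluded". The result is stated as "Hence, 30 studies from 1997 to 2017 were analysed". The stated purpose of the review was to extract outcomes from published trials of management, and the article calls the review comprehensive both here and in the Discussion.

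No later search is described. Under Trial status, "recruitment began on March 1, 2021".

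The search is not the only source. The same section closes with a second one, ahead of the Delphi: "In addition, we will develop a comprehensive inventory of outcomes in consultation with key stakeholders including healthcare professionals, researchers and individuals with lived experience". Under Round 1, participants may also propose outcomes; the steering group considers these and may put them into Round 2.

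**The concern.** A review that feeds a Delphi list has to find which outcomes trials have used. It does not estimate an effect, so the usual reasons for setting aside weak studies do not carry over. CONSORT is a reporting standard, and a poorly reported randomised trial still names what it measured. Lack of full text is also a weak ground for exclusion if the abstract names the outcomes. A search that ends more than three years before recruitment cannot pick up outcomes that trials introduced in the meantime.

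An outcome that is never listed cannot be scored and so cannot become core. The set is meant to apply to future RCTs, systematic reviews and guidelines, so a gap in the candidate list would be passed on to all of them. Rarely reported outcomes are the most exposed. In Table 1, three of the 18 rows (subsequent ectopic pregnancy, economic impact, psychological impact) rest on one trial each. Had that trial been among those set aside, the row would be absent.

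**Working it through.** **Inputs** (all from Identifying potential core outcomes, except the recruitment date, which is from Trial status): 89 records found; 30 off-topic; 25 removed on CONSORT grounds; 4 without full text; 30 analysed; search window to the end of 2017; recruitment from 1 March 2021.

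**The article's own figure.** 89 − 30 − 25 − 4 = 30. The flow closes.

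**Share of on-topic studies that contributed no outcomes.** On-topic studies: 89 − 30 = 59. The share depends on what the CONSORT exclusion meant. Let k be the number of the 25 that were randomised trials. Then

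share lost = (k + 4) / (30 + 4 + k)

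- k = 0 (none was randomised): 4 / 34 = 11.8%.
- k = 12 (about half, for illustration): 16 / 46 = 34.8%.
- k = 25 (all were randomised and were rejected on reporting): 29 / 59 = 49.2%, made up of 25 / 59 = 42.4% for CONSORT and 4 / 59 = 6.8% for access.

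**Age of the search.** From the end of 2017 to 1 March 2021 is 3 years and 2 months. The article gives the start of recruitment, not the date on which Round 1 opened, so the gap to Round 1 is at least this long if Round 1 did not precede recruitment.

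**What the exclusions could cost, for illustration.** Assume that an outcome is reported by a share p of trials, independently, and with the same p in the included and the excluded studies. Neither assumption can be checked from the article. The chance that n trials all fail to report it is (1 − p)^n:

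| p | n = 30 (as analysed) | n = 34 (adding the 4) | n = 59 (adding all 29) |
|---|---|---|---|
| 0.01 | 74.0% | 71.1% | 55.3% |
| 0.033 | 36.5% | 32.0% | 13.8% |
| 0.05 | 21.5% | 17.5% | 4.8% |
| 0.10 | 4.2% | 2.8% | 0.2% |

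The row p = 0.033 is close to the frequency of the rarest rows of Table 1 (1 in 30). For such outcomes, recovering the 25 would matter if they were randomised trials. Recovering only the 4 changes little. For common outcomes neither matters much. The number of outcomes actually lost cannot be computed from the article.

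**What happens to an outcome that arrives late.** Under Round 1, acceptance of a suggestion is left to the steering group. Under Round 2, accepted additions are scored there, and the 70/15% consensus definition is applied after that round. An addition would thus be scored once, while an original item is scored twice with feedback in between. The Stakeholder consultation section allows a further round if needed, and Trial status speaks of three rounds, so a second scoring is possible but not assured.

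**The case against.** The strongest reply is that the search is only one source. Stakeholder consultation, including people with lived experience, feeds the inventory before Round 1; the survey is piloted; and participants can propose outcomes. This stands. A reader might infer from the search alone that the Round 1 list is incomplete by design, and the article does not support that.

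A second tempting inference starts from Table 1, which has no row for maternal death or live birth although the Introduction relies on both. Table 1 lists what 30 trials reported. It is not the Round 1 inventory, which the article does not show. Nor does anything indicate that the excluded or later trials reported those two outcomes. The missing rows do not prove a gap in the Delphi.

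Third, the CONSORT wording may mean that the 25 were judged not to be RCTs. On that reading the objection to excluding them on reporting quality falls away. A reader might infer that half of the RCTs were discarded for poor reporting, but that is only the upper end of the range. It has some plausibility because the search was already filtered for RCTs. The article does not settle the matter, and the review is cited as a separate publication that may do so.

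What remains after these replies is that consultation does not retrieve what unread trials measured, that the literature source ends in 2017, and that late suggestions have a weaker route into the set.

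**Conclusion.** The literature component is dated and narrowed. It ends 3 years and 2 months before recruitment with no described update, and it leaves out between 11.8% (4 of 34) and 49.2% (29 of 59) of the relevant studies, on grounds that count for little when only outcome names are wanted. The upper figure assumes that all 25 CONSORT exclusions were randomised trials; the lower assumes that none was.

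The other sources offset this in part. No specific outcome is shown to be missing from the Delphi, and the effect on the final core set cannot be quantified. The point is therefore a cheap improvement to the candidate list. It does not invalidate the Delphi method or the consensus rule.

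**What to change.** 1. Rerun the same PubMed search from 2018 to the date on which Round 1 opens, and extract the outcome names.
2. State what the CONSORT exclusion meant and how many of the 25 studies were randomised. Extract outcome names from those that were, whatever their reporting quality.
3. Extract outcome names from the 4 studies without full text, where the abstract gives them.
4. Add every new outcome to the inventory before Round 1. If Round 1 is already open, add it in Round 2 and rescore it in a further round, which the Stakeholder consultation section already allows. Without the further round, these additions would have the same single scoring as late suggestions.

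The cost is one repeated query, a small amount of extraction from records largely already identified, and a slightly longer survey. If Round 1 is already open, the further round adds time to a schedule that expects completion in July 2021, although Trial status already counts three rounds.

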### Selecting core outcomes

Using the modified Delphi method, 3 key stakeholder groups including healthcare professionals, research clinicians and individuals with lived experience in ectopic pregnancy will be invited to participate and grade potential core outcomes. Participants are recruited widely across existing research networks and patient advocacy groups, and once consented to participate in the study, all stakeholders will receive email invitations, with a link to access the online Delphi study. Key stakeholders will rank outcomes from one (not important for decision making) to nine (critical for decision making), as well as suggesting further outcomes for study. This series of repeated surveys to key stakeholders allows for assessment of the extent of agreement and disagreement by facilitating repeated reflection and rescoring [12]. Furthermore, web-based scoring systems allow not only for a global level of participation, but also for ranking with anonymity, efficiency and feasibility. There are currently no clear recommendations for calculating the required sample size. Based on previous studies, we will aim to include a minimum of 16 participants from each of the key stakeholder groups [12–14].

### Delphi study pilot

A Delphi survey pilot will be developed using the Delphi Manager software to ensure feasibility and ease of completion for stakeholders using the appropriate and patient-friendly terminology. This Delphi study will be piloted by the study committee and a sample of stakeholders prior to being accessible to all stakeholders. This initial steering group was formed via email invitation through existing research networks.

### Round 1

During round one of the Delphi survey, all participants will be invited to provide their demographic details and will be provided with a unique identifier to facilitate responses to future rounds with anonymity. Outcomes will be listed in individual domains, and key stakeholders will be asked to score individual outcomes using the nine-point Likert scale, which was created by the Grading of Recommendations, Assessment, Development and Evaluation (GRADE) working group, and widely adopted by developers of core outcome sets [15]. Additionally, participants are invited to suggest additional outcomes before completing the first-round survey which will have a 4-week window for completion. All outcomes are summarised as a whole and for individual stakeholder groups using Delphi Manager. Any additional outcomes will be considered by the steering group and potentially included for review in round two.

### Round 2

All outcomes from round one will be then carried forward to round two and key stakeholders will receive individual stakeholder as well as group responses. Participants will be asked to reflect upon any similarities or differences between groups and then score each outcome again, as well as any additional outcomes suggested in round one, using the Likert scale. Following round two, each outcome will be summarised by whole and individual stakeholder responses. A standardised definition will be applied to results to identify core outcomes, as defined by the 70/15% consensus definition as advocated by the COMET initiative [16]. A consensus outcome would be identified when over 70% participants score the potential outcome as ‘critical for decision making’ (with a score of 7–9), and less than 15% of participants scored the outcome as being ‘of limited importance for decision making’ (with a score of 1–3).

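### Outcomes added after Round 1 meet the 70/15 rule on a single scoring without feedback, while outcomes on the Round 1 list have been scored twice with feedback

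*Protocol article*

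**What the plan says.** The sequence is set out in the protocol article under Delphi study pilot, Round 1 and Round 2.

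- **Round 1.** Listed outcomes are scored, and "participants are invited to suggest additional outcomes before completing the first-round survey which will have a 4-week window for completion". On those suggestions: "Any additional outcomes will be considered by the steering group and potentially included for review in round two".
- **Round 2.** On feedback, the article states: "All outcomes from round one will be then carried forward to round two and key stakeholders will receive individual stakeholder as well as group responses". After that, the panel is to "score each outcome again, as well as any additional outcomes suggested in round one, using the Likert scale".
- **Consensus rule.** On timing, the article says: "Following round two, each outcome will be summarised by whole and individual stakeholder responses". The next sentences apply the rule: more than 70% of participants scoring 7–9 and fewer than 15% scoring 1–3. No separate provision is made for outcomes that first appeared in Round 2.

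The section Selecting core outcomes gives the reason for a repeated survey: it "allows for assessment of the extent of agreement and disagreement by facilitating repeated reflection and rescoring". The abstract (Methods and analysis) gives the same reason and expects convergence from it.

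Two other places bear on the number of rounds. Stakeholder consultation lets the steering group suggest a further round if it sees a need. Trial status expects three rounds to be finished in July 2021.

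**The concern.** The same threshold is applied to two kinds of score. For an outcome on the Round 1 list, the score is a considered one, given after the participant has seen how the other groups and the whole panel responded. For an outcome added after Round 1, it is a first impression, because no earlier scores exist to be fed back. If feedback moves scores, as the protocol expects, the two are not comparable.

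What is at stake is fair selection for borderline outcomes. One that would have gained support on reflection may fail. One that would have lost support may pass. The outcomes exposed are those missed by both the literature review and the stakeholder consultation that precede Round 1.

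**Working it through.** **Step 1. Scoring and feedback occasions when the rule is applied (after Round 2).**

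| Outcome | Scored in Round 1 | Feedback before Round 2 | Scored in Round 2 | Scorings | Feedback steps |
|---|---|---|---|---|---|
| On the Round 1 list | yes | yes | yes | 2 | 1 |
| Suggested in Round 1 and accepted | no | none possible | yes | 1 | 0 |

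**Step 2. Does another section close the gap?** The further round under Stakeholder consultation has no stated trigger and no link to added outcomes. It is also mentioned in connection with the final meeting, after the rule has been applied. The third round in Trial status has no description in the methods. Nothing says that it rescores added outcomes or that the rule waits for it. So neither place closes the gap.

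**Step 3. Could one more scoring matter?** The protocol gives no figure to reproduce here, so this is an illustration.

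Inputs from the protocol: at least 16 participants in each of 3 groups, so n = 3 × 16 = 48; limits of over 70% and under 15%.

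Counts needed at n = 48:
- Scores of 7–9: 33/48 = 68.75% fails and 34/48 = 70.83% passes, so at least 34.
- Scores of 1–3: 7/48 = 14.58% passes and 8/48 = 16.67% fails, so at most 7.

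Assumptions: independent scorers, the rule applied to the whole panel, a true share p scoring 7–9 and a true share q scoring 1–3. Then

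P(pass) = Σ over a = 34 to 48 and b = 0 to min(7, 48 − a) of [48! / (a! b! (48 − a − b)!)] × p^a × q^b × (1 − p − q)^(48 − a − b).

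| Assumed p | Assumed q | P(pass both limits) | P(at least 34 score 7–9) |
|---|---|---|---|
| 0.65 | 0.10 | 0.243 | 0.246 |
| 0.70 | 0.08 | 0.517 | 0.521 |
| 0.75 | 0.07 | 0.795 | 0.800 |

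The last column shows that the 70% limit does nearly all the work. A rise of 5 points in p takes the chance of passing from about 24% to about 52%, and a rise of 10 points takes it to about 80%. Read from the bottom row up, the same table shows the effect of a fall. No document gives the size or sign of a feedback shift.

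**The case against.** The strongest reply has four parts.

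1. **Few outcomes are affected.** The section Identifying potential core outcomes ends by adding an inventory built in consultation with stakeholders, including people with lived experience, and that inventory enters the Delphi. Their outcomes can therefore be on the Round 1 list and be scored twice. This stands. A reader might infer that the set is tilted towards what trialists measured, or that Round 1 suggestions are the main way in for what trials overlooked. The protocol supports neither reading.
2. **The patient-experience outcomes are not at risk.** A reader might point to the low counts in Table 1 for psychological impact (1/30) and treatment satisfaction (4/30). Being in that table, they are already identified as potential outcomes and do not depend on suggestion. This stands.
3. **The rule is not the last step.** A consensus meeting reviews the results and may ask for another round. This softens the problem. It does not remove it, because the further round is discretionary and the meeting would still have only one set of scores for an added outcome.
4. **The numbers are assumed.** They are. They show that a modest shift can decide a borderline outcome. They do not show that it will.

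A reader might also see a contradiction between the steering group's discretion over suggestions in Round 1 and the wording in Round 2 that any additional outcomes are scored. Read in order, the two describe screening followed by scoring, so no contradiction is established.

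**Conclusion.** The point holds as one of unequal procedure. By the stated sequence, added outcomes reach the consensus rule with one scoring and no feedback, against two scorings and one feedback step for the Round 1 list. That conflicts with the protocol's own rationale for repeated rounds.

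The count of scorings rests on the text alone. The consequence for any outcome rests on assumptions: 48 scorers (the stated minimum, not an expected number), independence, and a feedback shift of 5–10 points. Under these, the chance of passing moves between about 24% and about 52–80% for a borderline outcome. Outcomes with a share well above or below 70% would be little affected. A claim that the final set is biased in a given direction goes further than the documents allow.

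This is worth correcting because the remedy is cheap and the timetable already counts a third round.

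**What to change.** Reconcile Round 2, Stakeholder consultation and Trial status so that they describe the same number of rounds. Specifically:

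- Make the third round firm and describe it in the methods.
- Feed back the Round 2 results, by group and overall, before it opens.
- Rescore at least the outcomes added after Round 1.
- Apply the 70/15 rule to an added outcome only once it has been scored twice, the second time after feedback.

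Rescoring only the added outcomes keeps the third survey short and brings every outcome to two scorings and one feedback step. Carrying all outcomes forward is also possible, but it lengthens the survey and gives the Round 1 list a third scoring, so some inequality would remain.

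The cost is protocol wording, a firm third round, some extra burden on respondents and possible attrition between Rounds 2 and 3. The number responding in each group should be reported for each round, so that a change in an added outcome's score can be told apart from a change in who answered.
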